#### fMRI scan

The acquisition will be carried out by the same professional and technical personnel in the magnetic resonance room of our hospital according to the prescribed acquisition sequence and parameters. Before the start of data collection, the contraindications of MRI examination will be checked again to see that the subjects do not have metal stents, pacemakers, etc., and the scanning steps will be introduced in detail, and the subjects will be instructed to lie flat on the scanning table in a resting and quiet state, and at the same time wear noise-canceling headphones to minimize the impact of the noise of the examination equipment on the collection results. During the scan, the subject will be asked to close his eyes and relax as much as possible, keep his head and body still, do not think or sleep, and start the scan after the subject is used to it. T1 structural image: the magnetization intensity will be used to prepare the gradient echo sequence, and the scanning parameters are as follows: time of repetition (TR) = 1900 ms, time of echo (TE) = 2.52 ms, field of view (FOV) = 250 mm × 250 mm, flipangle (FA) = 9°, matrix (Matrix) = 256 × 256, Thickness = 1.0 mm, Gap = 0 mm, voxel size = 1 × 1 × 1 mm^3^. rs-fMRI scanning: a gradient echo single excitation echo plane imaging is used, and the scanning parameters are: repetition time = 2000 ms, echo time = 13 ms, field of view = 192 mm × 192 mm, inversion angle = 90°, matrix = 64 × 64, layer thickness = 3.0 mm, layer spacing = 1 mm, voxel size = 3 × 3 × 3 mm^3^.

Data processing will be pre-processed with functional imaging data using resting-state functional magnetic resonance imaging software. Lesion size and fraction of anisotropy (FA) within the posterior internal capsule (PLIC) are determined by diffusion tensor imaging (DTI) to assess the integrity of the corpus callosum (CST). Anisotropy fraction (FA) values and mean anisotropy fraction asymmetry index (FAAI) are key indicators to assess bundle integrity (33, 34). DTI datasets will be processed using the Pipeline for Analyzing Brain Diffusion Images (PANDA) toolkit^1^ to obtain the average FA and FAAI values of patients from the whole group (35). The PANDA toolkit mainly includes the following steps: data preprocessing, diffusion tensor model fitting and index calculation, fiber tracing, brain structural network construction, and result output. Bilateral PLIC, Pontine and Anterior Gyrus will be selected as the target regions.

#### Data collection and management

In order to ensure the reproducibility, transparency and trust of the research, as well as to reduce data errors and biases, ensure data quality, and support accurate data analysis and reliable scientific conclusions, the study adheres to the following principles:

Ethics first: Ensure informed consent is obtained before data is collected, respecting privacy and cultural sensitivities. Comply with ethical review requirements to minimize potential risks to participants, the environment and society.Equitable access and inclusion: By avoiding improper exclusion in the participant recruitment process and formulating inclusion and exclusion criteria based on scientific reasons, we can ensure that the data collection objects are representative, avoid systemic bias, unswervingly follow FAIR principles, and promote Universality and fairness of research results.Quality first: Design a rigorous data collection plan, clarify the definition of variables and the collection process, and implement a real-time verification and cleaning mechanism to ensure the accuracy, completeness and consistency of data. Regular and rigorous monitoring of the trial will be carried out on the following aspects: division of work and training of researchers, file management, informed consent, protocol compliance, subject recruitment, intervention, statistical analysis, etc.

#### Data processing and analysis

We will use the Shapiro–Wilk test to assess whether the data are normally distributed. For data that conform to the normal distribution, it will be presented as means and standard deviations; for non-normally distributed data, it is presented as a median and interquartile range. For continuous data, one-way ANOVA will be used for between-group mean comparison; for categorical data, the chi-square test will be used for data analysis. The FMA-UE scale, BI score, NIHSS scale and imaging indicators [anisotropy score (FA) value and mean anisotropy score asymmetry index (FAAI)] will be analyzed by repeated measures ANOVA and multivariate ANOVA, respectively, in which the inter-group factors are high-frequency group, low-frequency group and sham stimulation group, and the intra-group factors are time (T0-T3), and multiple comparisons of LSD correction will be performed. The correlation between clinical scale data and imaging index data will be tested by Spearman or Pearson correlation tests. The level of statistical significance will be set at *p* < 0.05. In order to compare the therapeutic effects of different repetitive transcranial magnetic regimens, a two-factor mixed design analysis of variance including the inter-group factor “group” and the intra-group factor “time” will be used for clinical manifestations and electrophysiological changes. The DTI dataset will be processed via the PANDA toolkit to obtain the average FA and FAAI values for the entire population of patients.

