**Methods and analysis:**

This study will be designed as a randomized, sham controlled clinical trial. Thirty-six patients with upper limb motor dysfunction after stroke will be included, and their Fugl-Meyer Upper Extremity Motor Function Rating Scale (FMA-UE) score will be ≤ 26 points. Subjects will be randomly assigned to the following three groups (*n* = 12/group): HF-rTMS: Treated with high-frequency (5 Hz) repetitive transcranial magnetic stimulation (rTMS) on the dorsal premotor cortex (PMd) on the contralesional side. Low-frequency group (LF-rTMS): Treated with low-frequency (1 Hz) rTMS on the primary motor cortex (M1) on the contralesional side. Sham control group: The stimulation target and parameter settings will be the same as those of the high-frequency group, but the coil will be placed perpendicular to the scalp plane. The intervention regimen will be rTMS treatment once daily, five times a week for 3 weeks. Outcome measures: Main outcome measures: Upper limb motor function, assessed by FMA-UE. Secondary outcomes: Barthel Index (BI), National Institutes of Health Stroke Scale (NIHSS). Exploratory indicators: fMRI data and motor evoked potential (MEP) parameters. All assessment data will be collected before and after the intervention.

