### Participants and eligibility

#### Enrollment criteria

The following are the inclusion criteria: (1) meet the diagnostic criteria for stroke: according to the “Guidelines for the Diagnosis and Treatment of Cerebral Hemorrhage in China (2019)” or “Guidelines for the Diagnosis and Treatment of Acute Ischemic Stroke in China (2018),” the diagnosis is confirmed by head CT/MRI imaging; (2)characteristics of stroke attack: initial unilateral onset, or no sequelae of neurological deficit left by previous stroke attacks; (3) vital signs and consciousness state: Vital signs are stable for ≥ 24 h, Glasgow Coma Scale (GCS) score = 15 points;(4) age range: 18–75 years old; (5) upper limb motor deficit: baseline Fugl-Meyer Upper Limb Motor Function Rating Scale (FMA-UE) score ≤ 26 points (suggesting severe motor impairment) (18); (6) informed consent: Voluntary written informed consent; (7) Recruiting patients within 1 week to 6 months after stroke.

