#### Sample size calculations

In this study, in order to evaluate the effect of three different therapies on upper limb motor function rehabilitation in patients with severe stroke hemiplegia, the upper limb part of the Fugl-Meyer rating scale (FMA-UE) is used as the main efficacy index. The subjects are divided into high frequency group, low frequency group and sham control group according to the principle of random control. According to the relevant literature and pre-experimental results, the average FMA-UE of each group was 11.4, 4.7 and 2.8, and the standard deviation was 1.4, 0.9 and 1.3, respectively. When the *α* of the bilateral test value is 0.05 and the power of the power is 0.9, according to the PASS15 software “Means—One WayDesigns (ANOVA)—ANOVA-Test—One-Way Analysis of Varianc F-Tests,” it is calculated that at least 9 cases need to be enrolled in each group, and considering the shedding situation, according to the calculation of 20% dropout rate, at least 12 cases are needed in each group, A total of at least 36 participants are required in the three groups (24).

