## Discussion and conclusions

In recent years, many studies have confirmed that repetitive transcranial magnetism (rTMS) can effectively improve the motor function of stroke hemiplegic patients (36, 37). But there are also studies that have found negative results, and some patients even have functional degeneration (38, 39). These evidences suggest that standardized rTMS protocols based on the theory of bilateral primary motor cortex (M1) IHI imbalance have limitations in clinical practice (40). Patients with chronic stroke accompanied by severe motor impairments have widespread damage to the neural pathways in the affected hemisphere, resulting in the M1 region being unable to effectively promote motor function recovery, ultimately leading to the failure of repetitive transcranial magnetic stimulation (rTMS) therapy (41). Therefore, this study will focus on cPMd therapies based on the latest “bimodal equilibrium-recovery model” (12).

This study is the first to systematically evaluate the efficacy of high-frequency rTMS targeting the anterior dorsal motor cortex (cPMd) on the unaffected side on severe upper limb motor dysfunction after stroke. Based on the theoretical framework of the Bimodal Balance-Recovery Model (BBRM), we propose the following core mechanism hypothesis: when the corticospinal tract on the affected side is severely damaged, high-frequency stimulation of the unaffected side cPMd can significantly improve the recovery of motor function by enhancing transhemispheric compensatory nerve remodeling. This effect may involve: (1) reversal of inhibitory regulatory imbalance: regulation of pathological interhemispheric inhibition; (2) activation of compensatory pathways: promote synaptic plasticity of the unaffected hemisphere-spinal anterior horn network. The results of this study will provide key evidence for precision neurological rehabilitation: in the future, rTMS treatment plans need to stratify patients according to the time window of injury, lesion localization and CST integrity, so as to achieve individualized intervention. In addition, the cPMd high-frequency stimulation paradigm is expected to be extended to the neuromodulation of multi-domain dysfunctions such as aphasia and swallowing disorders after stroke.

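### The FMA-UE model treats baseline as an outcome level and names no covariate: valid under randomisation, but generally less efficient than a model adjusted for baseline and time since stroke

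*Protocol article*

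**What the plan says.** Under Data processing and analysis, FMA-UE, BI, NIHSS and the imaging indices "will be analyzed by repeated measures ANOVA and multivariate ANOVA, respectively". I read this as repeated-measures ANOVA for the scales and multivariate ANOVA for imaging. The between-patient factor is the three arms, and "the intra-group factors are time (T0-T3"). The section then restates the efficacy model for clinical and electrophysiological outcomes as "a two-factor mixed design analysis of variance including the inter-group factor" group and the within-patient factor time. Neither statement names a covariate.

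Four other places bear on the point:
- **Enrollment criteria:** "Recruiting patients within 1 week to 6 months after stroke", with baseline FMA-UE "score ≤ 26 points (suggesting severe motor impairment").
- **Randomization and blinding:** 1:1:1 allocation from a random number table; no strata are described.
- **Sample size calculations:** "according to the calculation of 20% dropout rate, at least 12 cases are needed in each group".
- **Abstract, Methods and analysis:** "All assessment data will be collected before and after the intervention". This reads as two time points, against the four implied by T0-T3. The schedule in Figure 2 is not available to settle it.

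**The concern.** A baseline score cannot be affected by treatment. Making it a level of the outcome has two consequences. The group main effect averages in a visit at which the true difference is zero. The group-by-time interaction compares changes from baseline, which fixes the weight on the baseline score at one instead of estimating it from the data. The article does not say which of the two effects carries the efficacy conclusion, so both matter.

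Time since stroke is a second baseline variable left unused. Recovery rate can be expected to differ between a patient at one week and one at six months. Change scores remove differences in starting level but not in recovery rate. With 12 patients per arm, an uneven mix of early and late patients is quite likely, and it would add noise to the comparison that neither planned test removes.

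At stake is the precision of the primary comparison in a trial that lists its small sample as a limitation. The model is named outright, so this questions a stated choice and not a detail left to an unseen analysis plan.

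**Working it through.** **Inputs from the article.** 36 patients, 12 per arm; time factor T0-T3 (Data processing and analysis) or before/after (Abstract); entry window 1 week to 6 months; 20% dropout. The dropout step reproduces: 9/0.8 = 11.25, rounded up to 12 per arm. The section on analysis gives no figure of its own to reproduce.

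**Assumed, because the article gives no value.** r, the baseline-follow-up correlation; k, the baseline SD divided by the follow-up SD; the share of early patients; the dropout mechanism.

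**1. Dilution of the group main effect.** Let the true difference be 0 at T0.
- One pre and one post visit: the main effect targets (0 + d)/2 = d/2.
- T0 plus three post visits with a constant difference d: (0 + 3d)/4 = 0.75d.
- T0 plus three post visits with a linear build-up to 3 points at T3: (0 + 1 + 2 + 3)/4 = 1.5. The three post visits alone average 2, so T0 again accounts for a factor of 0.75. The simulated means were 1.44 to 1.58.

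**2. Interaction against baseline adjustment, one pre and one post visit.** In units of the follow-up variance:
- Change score: 1 + k² - 2rk
- ANCOVA: 1 - r²
- Ratio, ANCOVA to change: (1 - r²)/(1 + k² - 2rk)

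With k = 1 this is (1 - r²)/[2(1 - r)] = (1 + r)/2:

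| r | ratio | SE reduction, 1 - √ratio | adjusted patients matching 36 under change scores |
|---|---|---|---|
| 0.5 | 0.75 | 13% | 36 × 0.75 = 27 |
| 0.7 | 0.85 | 8% | 36 × 0.85 = 30.6 |
| 0.9 | 0.95 | 2.5% | 36 × 0.95 = 34.2 |

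With k = r the denominator is 1 + r² - 2r² = 1 - r², so the ratio is 1 and there is no gain. In between, at r = 0.5 and k = 0.7, it is 0.75/(1 + 0.49 - 0.70) = 0.75/0.79 = 0.95.

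**3. Power by simulation.** 12 per arm, one pre and one post visit, a difference of 1 follow-up SD between two arms, r = 0.5:
- k = 1: group main effect about 26%, change score about 66%, ANCOVA about 76%.
- k = 0.7: change score and ANCOVA both about 75%.
- k = 0.5: change score about 77%, ANCOVA about 75%.

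**4. Imbalance in time since stroke.** Suppose 18 patients are early and 18 late, allocated at random 12/12/12. Exact counting gives a 15.8% chance that the high- and low-frequency arms differ by at least 4 of 12 early patients, and a 32.5% chance that some pair of arms does. The effect of such an imbalance on FMA-UE cannot be computed from the document.

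**5. Incomplete follow-up, if there are several post-baseline visits.** Classical repeated-measures ANOVA uses complete cases. At the planned 20% dropout that is 36 × 0.8 = 28.8, about 29 patients. A simulation with four visits, SD 6, a true difference of 3 points at T3 and about 20% dropout gave, for r = 0.5, 0.7 and 0.9:
- Dropout at random: both approaches average about 3.0. The SD of the estimate is 2.73, 2.11 and 1.26 for complete-case change, against 2.43, 1.97 and 1.24 for the baseline-adjusted mixed model.
- Dropout depending on early response in two arms and random in the third: complete-case change averages 2.42, 2.66 and 2.73; the mixed model averages 2.99, 3.05 and 2.98.

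**The case against.** The strongest reply is that nothing here is an error. Under randomisation the group-by-time contrast is unbiased with complete data or random dropout, and the interaction is the usual treatment test in such a design, so the weak main effect is not the natural comparator. That stands as to validity. It does not remove the dilution, since the article does not say which effect is used.

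A second reply is that the gain depends on equal variances. Entry caps FMA-UE at 26 on a 66-point scale, so a baseline SD below the follow-up SD is plausible and the gain could be small or nil. This also stands. Asymptotically, however, ANCOVA is never less precise than the change score; the most it loses here is the cost of a degree of freedom.

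Three stronger readings are tempting and are not supported:
- *That the plan drops incomplete patients.* The article does not say how they are handled. Use of complete cases is a property of the classical method, and the handling may be set out in a document not shown. With only one post-treatment visit, a dropout has no outcome under ANCOVA either, so about 29 of 36 remain both ways. The document gives no per-visit loss rate from which a smaller number could be derived.
- *That the protocol itself calls time since stroke decisive.* The Discussion says that, in future, "rTMS treatment plans need to stratify patients according to the time window of injury, lesion localization and CST integrity". That concerns individualised treatment after this trial and lists two other factors beside time.
- *That adjustment gives less bias in general.* Chance imbalance is not bias and is covered by the type I error rate. In the simulation, bias appeared only when dropout was made to depend on observed response and to differ by arm.

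**Conclusion.** The point holds as one of efficiency. The named model puts a pre-treatment visit into the outcome, which reduces the group main effect to half the post-treatment difference with two visits, or to three quarters of the post-baseline average with four. With two visits its interaction is a change-score test. Adjusting for baseline multiplies the variance of that comparison by 0.75 to 0.95 for r between 0.5 and 0.9, if baseline and follow-up variances are equal, and by 1 if the SD ratio equals r. Neither r nor that ratio is in the document, so the size of the gain is unknown. Time since stroke, spread over 1 week to 6 months, is neither stratified nor adjusted for; the benefit of including it cannot be quantified. The change is worth making because it is cheap and the trial is small, but the planned analysis is not invalid.

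**What to change.** Make the primary analysis a model of post-baseline FMA-UE on group, visit and group-by-visit, with baseline FMA-UE and time since stroke (for example log days) as covariates and a small-sample degrees-of-freedom correction. Use ANCOVA if there is only one post-treatment visit; the Abstract and the T0-T3 wording must be reconciled to settle which applies. Report adjusted mean differences with 95% confidence intervals, and use the same form for BI and NIHSS.

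If there are several post-baseline visits, fit the model by likelihood and include all randomised patients with at least one post-baseline score. This keeps partial follow-up in the analysis.

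The cost is analysis wording and one or two degrees of freedom. No new data are needed: baseline FMA-UE is an entry criterion, and time since stroke must be known to apply the entry window.

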### Outcome assessment

#### Primary outcome measure

The FMA-UE (Functional Motor Assessment Scale-Upper Extremity) will be used to assess motor function in the paralyzed upper extremity. A total of 10 items, including reflex activity, flexor muscle movement, extensor muscle movement, activity with common movement, dissociative movement, hyperreflexia, wrist stability, wrist movement, finger movement, coordination, and speed, are scored on a total of 66 points, with higher scores indicating milder dyskinesia (31).

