### Secondary outcome

#### Scale and electrophysiological assessment

Modified Barthel index (MBI): including 10 activities closely related to daily living, such as eating, bathing, grooming, and dressing, which are used to assess the ability of daily living activities, the higher the score, the higher the independence of the patient’s daily life, and the score greater than 60 indicates that the patient is likely to be able to complete the activities of daily living and maintain a normal standard of living (32).National Institutes of Health Stroke Scale (NIHSS Scale): It includes a multi-faceted evaluation of the patient’s state of consciousness, language, sensory and motor function, which is used to evaluate the degree of neurological deficit, and the higher the score, the more serious the patient’s neurological impairment.Motor evoked potential (MEP): Before and after treatment, the upper limb MEP is measured for the patient, first the upper limb on the unaffected side and then the upper limb on the affected side; The electrode is recorded by electrodes attached to the abductor pollicis brevis muscle, the reference electrode is attached to the tendon, connected to the ground wire, and transcranial magnetic single stimulation is performed in the functional area of the opposite hand of the tested limb to observe the waveform and the patient’s limb. The latency and amplitude are recorded.

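### The four-level time factor conflicts with the before-and-after schedule, and FMA-UE keeps at least two candidate tests with no deciding effect or time point

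*Protocol article*

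**What the plan says.** **Visits.** Under Data processing and analysis, the protocol article lists FMA-UE among the outcomes for which "the intra-group factors are time (T0-T3". The Methods and analysis paragraph of the Abstract states "All assessment data will be collected before and after the intervention". The text available here does not define T0, T1, T2 or T3 and mentions no interim or follow-up visit. Figure 2, the schedule, is not shown.

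**Outcome.** Under Primary outcome measure, the FMA-UE "will be used to assess motor function in the paralyzed upper extremity". No time point is attached, and the section does not say whether the score or its change is analysed.

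**Tests.** Three statements under Data processing and analysis can be read as covering FMA-UE:
- for continuous data, "one-way ANOVA will be used for between-group mean comparison";
- the scales and imaging indicators "will be analyzed by repeated measures ANOVA and multivariate ANOVA, respectively", followed by LSD comparisons;
- for clinical and electrophysiological changes, "a two-factor mixed design analysis of variance including the inter-group factor" of group and a within-patient factor of time.

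**Sample size.** The calculation uses the software's "One-Way Analysis of Varianc F-Tests".

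**Objective.** The Objectives section compares the high-frequency regimen on the contralesional premotor cortex (HF) with the low-frequency regimen on the contralesional primary motor cortex (LF).

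**The concern.** The number of visits determines what the group-by-time test is. If the document gives both two and four, the analysis of the primary outcome is not determined. The group effect, the interaction and a single-visit comparison are also different hypotheses, and nothing says which of them decides the trial.

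Two of these fit the objective poorly. A three-group F test can be significant because both active arms differ from sham, with no HF-LF difference at all. The group main effect in a mixed ANOVA averages over all visits including baseline, where randomisation makes the expected difference zero.

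At stake is the meaning of a positive result. If the choice is still open when the data are seen, several p-values are available for one endpoint and the nominal 5% level no longer describes the error rate.

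**Working it through.** **1. Visits side by side.** T0 to T3 is four labels; before and after is two occasions. If Figure 2 shows four visits, the Abstract is wrong for FMA-UE. If it shows two, the time factor is wrong.

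**2. How many tests really cover FMA-UE.** A repeated-measures ANOVA with a between-group factor and a time factor is the two-factor mixed ANOVA, so these are one model described twice. The multivariate ANOVA is probably meant for the imaging indicators, given the word respectively. That leaves two distinct tests: the one-way ANOVA and the group-by-time mixed ANOVA. The first can be run on the post-treatment score or on change. The second yields a group effect and an interaction.

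**3. Degrees of freedom of the interaction.** With k = 3 groups, n = 12 per group (Sample size calculations) and t visits:
- numerator df = (k - 1)(t - 1); denominator df = k(n - 1)(t - 1);
- t = 2: 2 × 1 = 2 and 3 × 11 × 1 = 33;
- t = 4: 2 × 3 = 6 and 3 × 11 × 3 = 99.

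For t = 2 the test is algebraically a one-way ANOVA on change. Simulated p-values from the two agreed to about 1e-15. For t = 4 it asks whether the groups' profiles differ anywhere over four visits, which is another hypothesis.

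**4. The plan's own numbers.** The step from 9 evaluable to 12 per group reproduces: 9 / (1 - 0.20) = 11.25, rounded up to 12, and 3 × 12 = 36. The 9 itself does not follow from the named F test. With means 11.4, 4.7 and 2.8 and the pooled SD √[(1.4² + 0.9² + 1.3²)/3] = 1.219, that test reaches 0.95 power with 2 per group. This is a separate matter and nothing here depends on it. What matters here is only that the sized test is a one-way F test.

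**5. Type I error if the choice stays open.** Simulation under no group effect: 40,000 trials per setting, normal data, four visits, equal correlation between visits. The correlations are assumptions; the article gives none.

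| Candidates, any p < 0.05 counts | 12 per group, correlation 0.5 | 12 per group, correlation 0.8 |
|---|---|---|
| ANOVA on post value alone | 5.0% | 4.9% |
| ANOVA on change alone | 5.0% | 5.0% |
| Four-visit interaction alone | 5.1% | 5.0% |
| Post value or change | 9.1% | 9.5% |
| Post value, change or four-visit interaction | 12.1% | 12.5% |

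With 9 per group the last row is 12.2% and 12.5%. The fourth row uses only the first and last visit, so the problem does not vanish if there are just two assessments.

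**The case against.** The case on the other side has weight.

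- **One model may be intended.** The one-way ANOVA sentence is generic, sits beside the chi-square test for categorical data, and may be meant for baseline comparability. FMA-UE would then have a single group-by-time model. This is possible, but the text does not say so, and the sample size rests on a one-way test. Even then, the deciding effect is unnamed.
- **The sized and planned tests may coincide.** With two visits, the interaction is the one-way ANOVA on change, and the planning means may be changes, although the article calls them averages. A reader might infer that the trial was certainly sized on a test that will not be run. The document does not support that; the mismatch follows from the four-visit reading.
- **HF versus LF is covered.** The LSD comparisons include it, so the objective is not left without any test. It is, however, one of several comparisons, with no priority and no visit attached.
- **Details belong in an analysis plan.** An unseen plan may name the primary effect and time point, and their absence alone would be no finding. It cannot remove the disagreement between the Abstract and the analysis section. Figure 2 cannot either; it can only show which of the two to correct.
- **The MEP sentence.** "Before and after treatment, the upper limb MEP is measured for the patient" concerns MEP only and is not evidence about FMA-UE visits.

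A reader might also infer that the choice of test costs power. Under the article's own planning figures it does not: HF minus LF is 11.4 - 4.7 = 6.7, or 6.7 / 1.219 = 5.5 SD, and every candidate test has 100% simulated power. Losses appear only under a smaller assumed effect and an assumed sham mean, so no power claim is made.

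**Conclusion.** The concern holds in this form. The document contradicts itself on the number of assessments, and it leaves the primary outcome with at least two distinct tests and no deciding effect or time point. Its HF versus LF objective is reached only through one unprioritised LSD comparison.

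The size is a type I error of about 12% instead of 5% if any of three candidate tests could be called the primary result. That figure is illustrative. It rests on normal data, equal correlation between visits (0.5 assumed; 0.8 gives nearly the same) and a free choice among those three tests. The article does not say that such a choice will be made; it fails to rule it out.

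A reader might count four competing ANOVAs for FMA-UE. The text does not support that count, since two of them are one model and the multivariate ANOVA is probably for imaging.

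**What to change.** 1. Make the Abstract and the analysis section agree on the assessment times, and define each label used for the time factor.
2. Name one primary analysis. Suggested wording: *The primary analysis compares FMA-UE at the end of the 3-week course between the high-frequency and low-frequency groups, as a two-sided 5% test of that contrast in an ANCOVA with group as factor and baseline FMA-UE as covariate.*
3. Label the omnibus F tests, the group-by-time interaction, any other visits and the contrasts with sham as supportive.
4. Restate the sample-size justification for that same contrast, and say whether the planning means are changes or post-treatment scores.

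The cost is wording, with no new data or visits, provided it is done before unblinding. The small downside is that the other tests can no longer be claimed as the primary result.

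### LSD is presented as a multiplicity correction, but it tests each pair at an unadjusted 0.05; it holds 5% only after a significant overall test at one visit, which the plan does not state

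*Protocol article*

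**What the plan says.** The section Data processing and analysis plans repeated measures and multivariate ANOVA for several measures: "The FMA-UE scale, BI score, NIHSS scale and imaging indicators", the last being FA and FAAI. The between-patient factor has three levels: "the inter-group factors are high-frequency group, low-frequency group and sham stimulation group". The within-patient factor runs over four labels: "the intra-group factors are time (T0-T3". The same sentence then says that "multiple comparisons of LSD correction will be performed". A single threshold applies throughout: "The level of statistical significance will be set at" p < 0.05.

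The text does not make the pairwise comparisons conditional on a significant overall test. It names no primary visit and does not say whether LSD is applied at each visit or to the group averages.

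Two other places bear on the point. The abstract names one main outcome ("Main outcome measures: Upper limb motor function, assessed by FMA-UE") and calls fMRI and MEP exploratory. It also states that "All assessment data will be collected before and after the intervention", which reads as two assessments, not four.

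**The concern.** LSD is a set of pairwise t tests, each at the nominal level. Calling it a correction tells the reader that multiplicity has been dealt with when the procedure makes no adjustment. Any control comes from a significant overall test carried out first, and that step is not written down. Even with it, the control covers one outcome at one visit and does not extend over repeated visits.

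At stake is a claim that one regimen differs from another, or from sham, resting on one of several unadjusted tests in a 36-patient trial. Low-frequency v sham is the most exposed comparison. It has the smallest assumed difference, and if the high-frequency arm works, any overall test will nearly always be significant and leave that pair tested at 0.05 wherever it is examined.

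**Working it through.** The protocol gives no family-wise error rate, so there is no stated figure to reproduce. The check asks what rate follows from the stated procedure.

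**Inputs from the protocol.** Three groups, hence 3 pairs; two-sided alpha 0.05; 12 enrolled and 9 evaluable per group; time labels T0 to T3; planning means 11.4, 4.7 and 2.8 with SDs 1.4, 0.9 and 1.3 (Sample size calculations).

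**Assumptions.** T0 is baseline, leaving three post-baseline visits. The documents give no correlation between visits, so 0.5, 0.7 and 0.9 are used.

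**Upper guide if tests were independent.** 1 − 0.95^k gives 14.3% for k = 3 and 37.0% for k = 9. The real tests share groups and patients, so simulation is needed.

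**Simulated rates, 12 per group, one outcome.** Two separate runs used 4,000 and 20,000 trials per setting. The Monte Carlo standard error near 12% is √(0.12 × 0.88/4,000) ≈ 0.5 percentage points for the smaller run.

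| Setting | Correlation 0.5 | 0.7 | 0.9 |
|---|---|---|---|
| 3 pairs, one visit, no prior test, all groups equal | 11.9 / 11.9% | 12.6 / 11.8% | 12.2 / 11.7% |
| 9 tests (3 pairs × 3 visits), no prior test, all groups equal | 28.8 / 28.1% | 25.9 / 24.6% | 19.4 / 18.8% |
| High-frequency shifted 1.5 SD, low-frequency equal to sham, significant interaction required first: any low-frequency v sham rejection | 12.2 / 12.3% | 10.7 / 10.7% | 8.3 / 8.7% |

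The correlation does not affect the first row; the spread there is simulation noise. A further run of the last setting gave 9–13%.

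**Where LSD does work.** With three groups, if any two pairs are equal then all three groups are equal. The closed family is therefore the overall null plus the three single pairs. Testing the overall null at 5% and then each pair at 5% is a valid closed test. Simulation agrees: with all groups equal, LSD after a significant F gives 5.0% at 12 per group and 5.3% at 9. With one group shifted, the remaining null pair is rejected 5.1% of the time.

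**Why this does not carry over to several visits.** When only the high-frequency arm differs, one true null (low-frequency v sham) remains at each visit. One significant interaction opens all three of those tests at 0.05. The independence guide is 1 − 0.95³ = 14.3%, and correlation brings it down to the 8–13% above.

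**Cost of requiring the overall test.** The grand mean is (11.4 + 4.7 + 2.8)/3 = 6.3. The squared deviations sum to 26.01 + 2.56 + 12.25 = 40.82. The mean variance is (1.96 + 0.81 + 1.69)/3 = 1.487. At 9 per group the noncentrality is 9 × 40.82/1.487 ≈ 247, and power is effectively 1; it already exceeds 0.999 at 3 per group. The smallest pair differs by 4.7 − 2.8 = 1.9 with pooled SD √((0.81 + 1.69)/2) = 1.118. A t test at 0.05 needs 9 per group for 90% power, so a prior overall test leaves that power practically unchanged. Bonferroni over the three pairs (0.0167) would instead need 11 evaluable, hence 11/0.8 = 13.75, i.e. 14 enrolled per group and 42 in total.

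**The case against.** The strongest reply is that LSD is a defensible choice for exactly three groups. The ANOVA is named first and LSD follows in the same sentence, so a reader may well take it as a follow-up to a significant F. For one outcome at one visit that holds 5%. A condensed article may leave such detail to the full protocol or analysis plan.

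Much of this stands. A reader might infer that LSD can never control error, or that having three groups is itself the source of inflation. The documents do not support that: the 12% arises only if no overall test comes first, which the text neither states nor excludes.

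The 19–29% needs more still: per-visit use of LSD and three post-baseline visits. The text does not say that LSD is applied visit by visit, and the abstract suggests a single post-treatment assessment. With one such FMA-UE comparison after a significant F, the rate stays at about 5%. The 8–13% is one scenario, with low-frequency exactly equal to sham, whereas the planning values have them differ. With all groups equal, requiring a significant interaction first keeps the rate over three visits at about 2–5%, for visit correlations from 0.8 down to 0.

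It would also be tempting to multiply the problem over all five measures. But FMA-UE is the only primary outcome, and unadjusted secondary or exploratory tests are acceptable if labelled as such.

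What the reply does not answer is the wording itself. The protocol names a procedure as its multiplicity correction, and that procedure makes no adjustment. This is a wrong statement, not a detail left for later.

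**Conclusion.** The point holds in limited form. The label is wrong, and the condition under which LSD would be valid is not written. The size depends on how the sentence is carried out:

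- about 5% with a prior overall test, one outcome and one visit;
- about 12% without that test at one visit;
- about 19–29% without it over three post-baseline visits, for correlations from 0.9 down to 0.5;
- about 8–13% for a false low-frequency v sham finding over those visits after a significant interaction, when the high-frequency arm differs by 1.5 SD and the other two are equal.

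The multi-visit figures rest on assumed correlations and on reading T0 to T3 as three post-baseline visits. They are not estimates of the error rate this trial will have. The finding calls for a correction of the text; it does not undermine the design.

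**What to change.** 1. Delete the word correction after LSD.
2. Name one primary FMA-UE time point, for example the end of the 3-week treatment. Test the overall group effect there at 5%, and do the three pairwise tests at 5% only if it is significant.
3. For FMA-UE at other visits, apply Holm across all those visits and pairs taken together, or label the comparisons exploratory. Adjusting within each visit alone would leave the multiplicity over visits in place: Tukey applied separately at each of four visits still gives 12–19%, for visit correlations from 0.8 down to 0.
4. Label the comparisons of BI, NIHSS, MEP, FA and FAAI as secondary or exploratory and not adjusted for multiplicity.
5. Reconcile T0 to T3 with the before-and-after schedule in the abstract.

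The cost is a few sentences and the choice of a primary time point. There will be slightly fewer rejections than with LSD used without a prior test. For the primary test that loss is negligible under the planning values, and no patients need to be added. Holm at the other visits makes those comparisons somewhat less sensitive.
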